**11. STATISTICS**

To analyse the number of patients with response or remission at three defined points in time (weeks 2, 9 and 29), Chi2 distribution is used. To do this, the Last Observation Carried Forward (LOCF) is employed. The assessment of the longitudinal courses of response and remission (and sustained response and remission) uses survival analysis (Kaplan-Meier survival-analysis) including log-rank test to calculate p values (Stassen et al 1993). Furthermore, the Mixed Model Repeated Measures (MMRM) (Brown et al. 1999) will analyse readily available depression scores to determine the difference between the two groups. Thus, MMRM does not use LOCF. The association between cortisol and depression scores and the association between urine and saliva cortisol has been calculated by means of the Spearman correlation coefficient *rho*. The same statistical method will be used to test the association between the various degrees of depression and the effect of sleep deprivation. The idiographic method will be analysed by means of MMRM. Exercise will be analysed as the percentage of compliance to the predefined goal (30 minutes exercise daily). Moreover, the achieved amount of exercise (combined score of the Borg scale and the amount of performed exercise) will be graded into light/moderate/intensive in follow-up phase I. It will be compared with the degree of response and remission in week 29 and analysed by Chi2 distribution. The number of study subjects has been calculated on the basis of an expected depression score of 24 on the 17-item Hamilton Depression Scale at inclusion into the study for both groups. After 9 weeks of treatment a decrease to 10 in group A and to 13 in group B is expected. The expected standard deviation is 4. With a type-I error of 0.05 and 0.90 power, 39 patients are required for each group.

No interim analyses have been planned.

GCP guidelines permit that patients may be excluded from the data analysis after the end of the study, if eligibility violations have taken place and if this was not known during the project. This may refer patients who have fulfilled the inclusion criteria, but have not taken any of the study medication, or have taken other prescriptions without telling the investigator, and where these violations were not known until the end of the study. All other patients assessed at the time of inclusion in the study are included in the statistical analyses according to the intention-to-treat method.

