4.6.5. Criteria for discontinuation of study treatment (end-points)

- The wish to discontinue treatment (sufficient follow-up treatment will be secured). In case of a waiting period treatment will be provided by the Psychiatric Research Unit.
- Patients with intolerable or clinically significant side effects.
- Patients who at any time during the first 9 weeks of the study have score of 15 or more on the Mania Scale (MAS) irrespective of a mania or hypomania diagnosis.
- Patients who display a continued clinical worsening of their depression at two subsequent weekly assessments (first nine weeks of the study).
  - Patients who after the primary hospitalisation experience a worsening of their depression and have to be re-admitted (first 9 weeks).
  - Mania requiring hospitalisation (first 9 weeks).
  - Change of mood stabilizer in bipolar patients (whole study).
  - Patients who do not comply with the single elements of the study will in general be discontinued (but see also "protocol deviations")

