**12. DIMENSION**

According to the expected results of the study (see power calculation in the statistics section) and taking into account the possibility to analyse subgroups such as unipolar and bipolar patients, it is intended to include 100 patients into the study, 50 to each group. The patients are included consecutively and it will thus not be possible to foretell how many bipolars and how many unipolars will have been included at the end of the study.

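### The Kaplan-Meier and log-rank analyses of response have no rule for patients taken out for worsening, re-admission or mania; if they are censored by default, the curves overstate response and can overstate its durability

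*Protocol*

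**What the plan says.** Section 11 assigns two kinds of analysis to response and remission. The numbers at weeks 2, 9 and 29 go to a chi-square test, for which "To do this, the Last Observation Carried Forward (LOCF) is employed". The longitudinal course, including sustained response and remission, "uses survival analysis (Kaplan-Meier survival-analysis) including log-rank test to calculate p values". Section 11 also commits to intention-to-treat.

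Section 4.6.5 lists reasons for discontinuation that depend on the patient's course. One is "Patients who display a continued clinical worsening of their depression at two subsequent weekly assessments (first nine weeks of the study". Another covers patients who, after the primary hospitalisation, "experience a worsening of their depression and have to be re-admitted (first 9 weeks". Two more concern mania: a Mania Scale score of 15 or more, and mania leading to admission. All four are limited to the first 9 weeks. The heading of 4.6.5 speaks of study treatment, but section 4.2 treats the Mania Scale threshold as exclusion from the study, and 4.6.6 speaks of ending participation.

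For a patient who leaves, section 4.6.6 lets an individual decision choose between the exit visit and the previous regular visit, and makes collection of last-visit data conditional on medication compliance. It also has the reason for drop-out recorded in the CRF.

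Section 4.3.2 does write a failure rule for one event after randomisation: patients given the additional sleep deprivations cannot be classed as in early lasting remission. No similar rule exists for the exits in 4.6.5.

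**The concern.** Kaplan-Meier and the log-rank test treat a censored patient as having the same later chance of the event as those still followed. A patient removed for worsening is not like that.

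- **Time to response or remission.** The exit prevents the event from being seen in the trial. If it is censored, the estimator spreads that patient's weight over those who stayed, who are doing better. LOCF keeps the same patient as a non-responder, so two analyses in section 11 would give different answers on the same people.
- **Sustained response or remission.** Worsening and re-admission are close to being the loss itself. If the loss was not scored before exit, or if the earlier visit is kept under 4.6.6, the patient leaves the curve as a censored responder.

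The stake is real because section 3 makes faster onset and lasting response the main objective, and these curves speak to it directly. Section 4.3.2 makes lasting response and remission the secondary parameter.

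**Working it through.** **1. The plan's own figure.** Section 11 assumes week-9 means of 10 (A) and 13 (B) with an SD of 4, and concludes: "With a type-I error of 0.05 and 0.90 power, 39 patients are required for each group". For a difference of 3, SD 4 and two-sided alpha 0.05:

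n = 2 × (1.960 + 1.282)² × 4² / 3² = 37.4, so 38 per group.

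The t-test version gives 38.3, so 39. The stated figure reproduces, and it rests on mean scores, so nothing below changes it. Section 12 plans 50 per group.

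**2. Response rates implied at week 9.** The protocol states none. With its baseline of 24, a reduction of more than 50% means a score below 12. Assuming normal scores:

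- Whole-number scores of 11 or less, cut at 11.5: A = Φ((11.5 − 10)/4) = 65%; B = Φ((11.5 − 13)/4) = 35%.
- Cut at 12: A = Φ(0.5) = 69%; B = Φ(−0.25) = 40%.

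**3. Time to response, exits censored.** Let E be the share who respond and C the share withdrawn before responding, with constant hazards. The total hazard is −ln(1 − E − C), the event share is E/(E + C), and

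1 − KM = 1 − exp{ln(1 − E − C) × E/(E + C)}.

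Example, E = 0.65 and C = 0.10: ln 0.25 = −1.386; × 0.8667 = −1.201; 1 − exp(−1.201) = 69.9%.

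| C (assumed) | A, true 65% | B, true 35% |
|---|---|---|
| 5% | 67.3% | 36.0% |
| 10% | 69.9% | 37.2% |
| 15% | 73.0% | 38.4% |
| 20% | 76.6% | 39.8% |

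A second calculation spreads events and exits evenly over the 8 weekly visits of weeks 2 to 9. At each visit S is multiplied by 1 − (E/8)/Y, and the number at risk Y then falls by (E + C)/8. Starting from 69% and 40%, C = 10% gives 73.8% and 42.3%. Over C = 5% to 20% the readings run from 71.3% to 80.4% in A and from 41.1% to 45.0% in B. Both calculations put the bias at 10% near 5 points in A and 2 in B.

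Scale: the standard error of one proportion is √(0.65 × 0.35/50) = 6.7 points, half of which is 3.4. For the difference it is √(2 × 0.65 × 0.35/50) = 9.5 points, half of which is 4.8.

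**4. Group difference.**

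| Withdrawn A / B | From 65 v 35 (true 30) | From 69 v 40 (true 29) |
|---|---|---|
| 10% / 10% | 69.9 − 37.2 = 32.7 | 31.6 |
| 15% / 5% | 73.0 − 36.0 = 36.9 (unrounded inputs) | 35.7 |
| 5% / 15% | 67.3 − 38.4 = 28.9 | 27.7 |

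**5. Sustained response.** Suppose 20% lose response on score alone and a further 15% are withdrawn for worsening, so true loss is 35%. Let f be the fraction of that 15% whose loss was scored, and kept, before exit. Then E = 0.20 + 0.15f, C = 0.15(1 − f), and −ln 0.65 = 0.431:

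- f = 0: 1 − exp(−0.431 × 0.20/0.35) = 21.8%
- f = 0.5: 1 − exp(−0.431 × 0.275/0.35) = 28.7%
- f = 0.8: 1 − exp(−0.431 × 0.32/0.35) = 32.6%
- f = 1: 35%

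The understatement of loss therefore runs from about 13 points to none, depending on a step the protocol leaves open.

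**The case against.** **No censoring rule is written.** A reader might infer that the protocol censors these patients. It does not say so; event and censoring definitions often sit in an analysis plan, and section 11 commits to intention-to-treat. This stands, so the point is conditional on the method's default. It remains worth raising because the protocol itself fixes the estimator, the test and the outcome-dependent exits, and section 4.3.2 writes a failure rule for a milder event but none for these.

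**Durability may look after itself.** Worsening must show at two weekly assessments and HAM-D17 is scheduled at every visit, so many responders would cross the threshold before leaving. This stands in part. It fails where the previous regular visit replaces the exit visit, or where re-admission comes before a scored loss. The gap of 21.8% against 35% is the extreme, not the expected result.

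**The illustration assumes every withdrawal precedes response.** With 65% responding, 15% withdrawn means 15/35 = 43% of group A's non-responders. A patient withdrawn after first response causes no bias in that curve. This stands; the upper end of the range is demanding.

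**Log-rank is not wrong in itself.** With competing exits it compares cause-specific hazards, which is a legitimate question. Insisting on Gray's test would be a choice of estimand, not the correction of an error.

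**Mania is not a HAM-D17 loss.** Section 4.3 defines response and remission on HAM-D17 alone, so counting mania as loss of response would redefine the outcome. This stands and shapes the fix.

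**Conclusion.** The point holds in conditional form. Kaplan-Meier is paired with outcome-dependent exits and a discretionary choice of last data, with no rule that these exits are failures. Under default censoring the response curves are too high, by about 5 points in group A and 2 in group B at 10% withdrawn, and by about 2 points in A and 1 in B at 5%. The durability curves are too favourable to the extent that loss went unscored or was discarded.

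These sizes rest on an assumed 5-20% withdrawn before response, on normal scores, and on response rates derived from the protocol's means and SD rather than stated there.

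Three stronger readings are not supported:

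- That the bias favours group A. The difference can be inflated or shrunk. The protocol's expectation of a slower effect from exercise would, if anything, suggest more exits in group B, which is the direction that shrinks it. With equal 10% withdrawal the shift of 2.7 points is below half a standard error of the difference.
- That the week 2, 9 and 29 results are compromised. The chi-square/LOCF counts involve no censoring.
- That the exits operate throughout the study. The four criteria apply only in the first 9 weeks, although patients lost then still affect the curves to week 29.

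**What to change.** Add to section 11:

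1. **Time to response or remission:** patients withdrawn under 4.6.5 for worsening, re-admission for worsening, or mania stay in the risk set as non-responders to week 29. Equivalently, report cumulative incidence with these exits as competing events. This agrees with the LOCF counts.
2. **Sustained response or remission:** withdrawal for worsening, or re-admission for worsening, counts as loss on the exit date.
3. **Last data:** use the exit-visit HAM-D17 whenever one exists, replacing the case-by-case choice in 4.6.6 for these analyses.
4. **Mania exits in the sustained analyses:** show as a separate competing event, with a sensitivity analysis counting them as loss.

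Log-rank may be kept on data coded this way; Gray's test is optional.

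The cost is a few sentences and a few lines of code. Drop-out reasons are already recorded in the CRF, and neither the sample size nor any clinical criterion changes. Response and durability estimates will come out slightly less favourable.

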**3. OBJECTIVE**

The main objective of the trials is to examine whether sleep deprivation in combination with light treatment, duloxetine and maintenance of diurnal rhythm (Group A) is able to induce a faster onset of action and lasting antidepressive response compared to an individually designed exercise programme in combination with treatment with duloxetine (Group B).

Secondary objectives are studies of cortisol concentration, variability of the degree of depression, the idiographic method and finally, applicability and effect of exercise over 9 weeks under supervision. The following hypotheses ar going to be tested in the study:

- Is sleep deprivation in combination with duloxetine, light and maintenance of diurnal rhythm (Group A) able to induce a greater degree of response or remission than exercise in combination with duloxetine (Group B). The hypothesis is tested after 2, 9 and 29 weeks of therapy?
- Is it possible for patients with major depression during the supervised course of treatment of 9 weeks to achieve the National Health Board's recommendation of exercising 30 minutes per day, and is there any association between the exercise effort and the degree of depression after 29 weeks?
- Is the cortisol concentration as measured in urine and saliva the beginning of week 2 correlated to the severity of depression as measured after 2, 9 and 29 weeks of therapy?
- Is the concentration of cortisol measured in saliva correlated with the concentration of cortisol in diurnal urine?
- Is the idiographic method more sensitive to change of degree of depression than clinician- and patient-rated scales and questionnaires for depression?
- Can variability in the degree of depression as measured with the Preskorn scale (see psychometrics) predict response to sleep deprivation?

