To decide at which hour light treatment should be administered, the Morningness-Eveningness Questionnaire (MEQ) will be used (Horne et al. 1976, Horne et al. 1977, Terman et al 2005).

Side effects will be rated by means of the UKU (Udvalget for Kliniske Undersøgelser, evaluation form for side effects) (Lingjærde et al. 1987), with relevant questions concerning serotonergic and noradrenergic side effects.

The Mania Scale (MAS) is to be used at all visits to assess the possible development of a hypomanic or manic condition. A MAS score of 15 or more thus means exclusion from the study.

The SPAQ (Seasonal Pattern Assessment Questionnaire) (Kasper et al 1989) questionnaire will be used to assess seasonal variability of the depression.

The idiographic method is to be used at all visits, but only in group B patients. The method implies free constructs by the patients who describe the symptoms they have experienced in connection with their current depressive episode. At each visit, the free construct is given as a percentage value in relation to the baseline construct (set 100% for each construct at baseline, e.g. how much of 100% tiredness is your tiredness today?), thus measuring change from inclusion an onwards. In contrast to the other scales used in the study, this method is not an absolute measure of severity. With this method we hope to obtain a more balanced picture of the symptoms we obtain by standardised methods such as questionnaires and rating scales, and we also hope to accomplish a greater degree of sensitivity towards change in the condition. The strength of this method is that symptoms which patients have experienced during their depression are not forced into the standardised boundaries of a rating scale or a questionnaire. The method is based on Kelly's ideas on free constructs (Kelly, 1955). It has been used in GRID-QOL (Thunedborg et al 1995), a computer-assisted quality of life rating system.

At inclusion, sleep and exercise are evaluated for both groups. Sleep diaries, exercise diaries and medication diaries are completed in both groups at each visit. Light diaries are only completed in group A.

The scales are employed as indicated in flowcharts 1 and 2. Flowchart 1 covers the first 9 weeks while flowchart 2 covers weeks 10 to 29.

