4.3.3 Tertiary effect parameters are

- The extent of exercise in follow-up periods I and II, measured as a combined assessment of the exercise effort by the Borg scale and an external evaluation.
- Cortisol concentration at inclusion (in saliva or diurnal urine) compared with cortisol after 2, 9 and 29 weeks.
- The cortisol concentration in diurnal urine at inclusion is compared with the cortisol concentration in saliva at inclusion.
- The percentage of variability of depression severity at week 0 (calculated from the Preskorn scores during the first 6 days of the study) is compared to change in depression severity after the 3 sleep deprivations at week 2.
- In treatment group B, the idiographic effect parameter is the percentage change from inclusion to week 29.

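### The plan asks whether the idiographic method is more sensitive to change than the rating scales, but its declared parameter and analysis contain no rating scale to compare it with

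*Protocol*

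**What the plan says.** Three statements in the protocol bear on this.

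- **The question (section 3).** Among the hypotheses to be tested: "Is the idiographic method more sensitive to change of degree of depression than clinician- and patient-rated scales and questionnaires for depression".
- **The parameter (section 4.3.3).** "In treatment group B, the idiographic effect parameter is the percentage change from inclusion to week 29".
- **The analysis (section 11).** "The idiographic method will be analysed by means of MMRM". Nothing further is said about it.

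Section 4.2 describes the measure. "The idiographic method is to be used at all visits, but only in group B patients". Patients name their own symptoms, each starting value is fixed ("set 100% for each construct at baseline"), and later visits are scored relative to it. The section adds: "In contrast to the other scales used in the study, this method is not an absolute measure of severity".

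The comparators are available. Flowcharts 1 and 2 schedule the Hamilton scale, MES, MDI and SCL-92 at inclusion, week 9 and week 29, and the idiographic method at the same three points. HAM-D6 is a subscale of the Hamilton scale (section 4.2).

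**The concern.** The hypothesis compares instruments, so its null is equal sensitivity to change. The parameter and the analysis, read together, involve one instrument. Because only Group B uses it, no contrast between arms is possible either. What remains is change over time from a starting value of 100%, which shows whether patients improved.

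The protocol expects them to improve. If improvement alone produces a clear result however sensitive the method is, that result carries no information on the question in section 3. Group B patients would have completed an extra instrument throughout the study for a hypothesis that the written plan cannot answer.

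**Working it through.** **Inputs from section 11.** The assumed mean HAM-D17 at the start is 24 in each arm. For the later value the section says: "After 9 weeks of treatment a decrease to 10 in group A and to 13 in group B is expected". Further inputs are SD 4, alpha 0.05, power 0.90 and 39 per group. Section 12 plans 50 per group. No week 29 mean is given, so I use the week 9 fall in Group B: 24 − 13 = 11 points.

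**The plan's own figure.** n = 2 × (1.960 + 1.282)² × 4² / 3² = 37.4, so 38 by the normal approximation. The two-sample t-test gives 38.35, so 39. The stated 39 reproduces, two-sided. No sample size is stated for the idiographic question.

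**Size of the expected change.** The standardised response mean (SRM) is mean change / SD of change, and SD of change = 4 × √(2(1 − r)). The within-patient correlation r is not in the protocol; I assume 0 to 0.5.

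- r = 0: SD 5.66, SRM = 11 / 5.66 = 1.94
- r = 0.3: SD 4.73, SRM = 11 / 4.73 = 2.32
- r = 0.5: SD 4.00, SRM = 11 / 4.00 = 2.75

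**What a test of the idiographic score's own change shows.** A one-sample t-test stands in for the MMRM time effect; its non-centrality is SRM × √n. For a much smaller change, SRM 0.7 with n = 50, it is 0.7 × 7.07 = 4.95 and power is 99.8%. The table gives simulated results (4,000 runs per case, n = 39 and 50, all three values of r). The last two columns come from a head-to-head test of the SRMs in the same patients, assuming a correlation of 0.6 between the two instruments' changes and normally distributed changes.

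| Idiographic sensitivity relative to HAM-D17 | Own change significant | Head-to-head: idiographic better | Head-to-head: idiographic worse |
|---|---|---|---|
| Equal | 100% | 2.7% to 3.5% | 2.4% to 3.3% |
| Three-quarters | 100% | 0% to 0.1% | 47% to 64% |
| Half | 100% | 0% | 98% to 99.9% |
| One quarter | 84% to 99.7% | 0% | 100% |

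The test of own change barely separates these four situations. The head-to-head test does.

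**Which head-to-head comparison.** The idiographic score is a percentage of the patient's own baseline, so I checked whether setting it against raw HAM-D17 change is fair. Let the percentage score be the HAM-D17 itself divided by the patient's own baseline, so that it holds no extra information. With n = 50, mean SRMs (percentage v raw) are 2.27 v 2.00, 2.68 v 2.37 and 3.08 v 2.79 at r = 0, 0.3 and 0.5. A paired SRM test with jackknife standard error then declares the percentage score more sensitive in about 53%, 50% and 29% of runs, against a nominal 2.5%. With independent measurement noise on each instrument the rate is about 13% to 17%, moving with the noise assumed. With both instruments as a percentage of own baseline it returns to about 3% to 4%.

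**The case against.** Section 11 names no response variable, factors or contrast for this MMRM. A mixed model can carry instrument as a within-patient factor, and details of that kind for a tertiary parameter are often left to an analysis plan, which is not at hand. Section 4.3.3 lists the percentage change as an effect parameter and does not call it the test of the section 3 hypothesis.

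Part of this stands. The response variable is inferred by reading section 11 with section 4.3.3. A reader might go further and infer that the trial will declare the idiographic method superior whenever Group B improves. The documents do not support that: nowhere do they say that a significant change over time would be taken as greater sensitivity, and they state no null hypothesis for this model.

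It does not remove the point. The protocol is not silent: it fixes a parameter and a method, and neither contains a second instrument. Where section 11 intends a contrast it says so, as with the depression-score MMRM for the difference between groups. An analysis plan that followed both sections would inherit the mismatch. Even a model with instrument as a factor would need a common metric, because section 4.2 says the method does not measure severity absolutely.

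**Conclusion.** The point holds as a mismatch between the question and the declared analysis. Read together, sections 4.3.3 and 11 describe the course of one score in one arm. At the expected improvement a test of that course is near-certain to be significant whether the method is as sensitive as HAM-D17 or half as sensitive, and likely even at a quarter (84% to 99.7%). It therefore cannot support or refute the hypothesis.

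The percentages rest on the week 9 expectation for HAM-D17, the assumed correlations and a t-test in place of the MMRM; the conclusion was the same across the range tried. The consequence is limited: this is a secondary objective with a tertiary parameter, no data are lost, and the primary comparison of A with B and its sample size are unaffected.

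**What to change.** In sections 4.3.3 and 11, add a within-patient comparison of responsiveness in Group B:

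- Compare the idiographic score with HAM-D17 as lead comparator, then HAM-D6, MES, MDI and SCL-92, from inclusion to week 9 and from inclusion to week 29.
- Express every instrument as a percentage of the patient's own inclusion score before computing the SRM. Do not set the percentage score against raw scale change, which favours the idiographic score by construction.
- Give a paired bootstrap or jackknife 95% confidence interval for the difference in SRM, and conclude that the method is more sensitive only if the interval lies above zero.
- Keep the MMRM as a description of the idiographic course.

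The cost is analysis wording only, since all the scales are already scheduled at these visits. Two downsides should be stated. First, the result may be inconclusive for modest differences. With n = 50, normally distributed changes and a correlation of 0.5 to 0.7 between the instruments' changes, power is about 49% to 66% for SRM 2.6 v 1.94 and 76% to 91% for 2.9 v 1.94. Second, limits on interpretation remain: patients choose the symptoms, the baseline is fixed at 100%, and under section 4.1.1 only the Hamilton rating is blinded, so a difference from HAM-D17 could partly reflect rating conditions.

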| **Study period and duration** | **Medication start phase:**  **7 days** | **Hospitalisation:**  **7 days**  Visits on week days | **Follow-up phase I:**  **7 weeks**  **Visits each week** | | | | | | | |
| --- | --- | --- | --- | --- | --- | --- | --- | --- | --- | --- |
| **Week no.** | **0** | **1** | **2** | **3** | **4** | **5** | **6** | **7** | **8** | **9** |
| **Visit no.** | **1 (Inclusion)** | **2** | **3** | **4** | **5** | **6** | **7** | **8** | **9** | **10** |
| **M.I.N.I.+ SCID I and II**  **SPAQ + MEQ + DIAD + SPS** | x |  |  |  |  |  |  |  |  |  |
| **Hamilton + MES + MAS + MDI + UKU + WHO-5** | x | x | x | x | x | x | x | x | x | x |
| **Preskorn** | daily | daily | daily | daily | daily | daily | daily | daily | daily | daily |
| **Borg scale + external assessment (exercise)** |  | x | x | x | x | x | x | x | x | x |
| **SCL-92** | x | x | x | x | x | x | x | x | x | x |
| **Idiographic method (gr. B)** | x | x | x | x | x | x | x | x | x | x |
| **EKG + Blood pressure + Blood samples** | x |  |  |  |  |  |  |  |  | x |
| **Collecting diurnal urine (gr. B)** |  | x |  |  |  |  |  |  |  |  |
| **Saliva samples (gr. B)** |  | x |  |  |  |  |  |  |  |  |
| **Sleep, light, medication and exercise diaries and status** | x | x | x | x | x | x | x | x | x | x |
| **Stanford Sleepiness Scale** |  | x |  |  |  |  |  |  |  |  |
| **Expectation to treatment** | x |  |  |  |  |  |  |  |  |  |
| **Evaluation of treatment** |  |  | x |  |  |  |  |  |  | x |
| **TEMPS-A** |  |  |  |  |  |  |  |  |  |  |

**Flowchart 1(week 0 to 9, duration 9 weeks**)

| **Study period and duration** | **Follow-up phase II:**  **20 weeks**  **Visit every 4th week** | | | | | |
| --- | --- | --- | --- | --- | --- | --- |
| **Week no.** | **9*** | **13** | **17** | **21** | **25** | **29** |
| **Visit no.** | **10** | **11** | **12** | **13** | **14** | **15** |
| **M.I.N.I.+ SCID I and II**  **SPAQ + MEQ + DIAD + SPS** |  |  |  |  |  |  |
| **Hamilton + MES + MAS + MDI + UKU + WHO-5** | x | x | x | x | x | x |
| **Preskorn** | weekly | weekly | weekly | weekly | weekly | weekly |
| **Borg scale + external assessment (exercise)** | x | x | x | x | x | x |
| **SCL-92** | x | x | x | x | x | x |
| **Idiographic method (gr. B)** | x |  |  |  |  | x |
| **EKG + Blood pressure + Blood samples** | x |  |  |  |  | x |
| **Collecting diurnal urine (gr. B)** | x |  |  |  |  | x |
| **Saliva samples (gr. B)** |  |  |  |  |  |  |

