**4.3. Efficacy parameters**

4.3.1 The primary efficacy parameter is the number of patients in the two group that have achieved response to treatment or remission after 2, 9 or 29 weeks. Response is defined as a more than 50% reduction in HAM-D17 scores after inclusion into the study while remission is defined as a score of 7 or less on the HAM-D17.

4.3.2. Secondary effect parameter is the number of those patients in the two treatment groups who have experienced long-lasting response or remission after 9 weeks and after 29 weeks. Lasting response is defined as patients responding after 2 weeks of enrolment in the study and the response either lasting until week 9 (early lasting response) or until week 29 (episode response). Lasting remission is defined as being in remission after 2 weeks in the study and the remission either lasting until week 9 (early lasting remission) or until week 29 (episode remission). Response and remission are defined as mentioned under primary efficacy parameter. Patients who according to the protocol receive further sleep deprivations in week 4, 5, or 6 thus are cannot be defined as being in early, lasting remission. Response and emission are defined as mentioned under primary efficacy parameter. Patients who according to the protocol carry out additional sleep deprivation in weeks 4, 5 or 6 thus are defined not to be in early lasting remission.

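### The exercise–depression association is tested through three exercise grades against response/remission categories, which addresses degree of depression only coarsely and loses power (minor)

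*Protocol*

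**What the plan says.** Section 3 lists among the hypotheses to be tested: "is there any association between the exercise effort and the degree of depression after 29 weeks". Section 4.3.3 makes the extent of exercise a tertiary parameter.

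Section 11 fixes the analysis. The achieved amount of exercise, a score combining the Borg scale with the exercise performed, "will be graded into light/moderate/intensive in follow-up phase I". Then: "It will be compared with the degree of response and remission in week 29 and analysed by Chi2 distribution". Compliance with the goal of 30 minutes a day is also analysed, as a percentage, but is not linked to depression.

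Section 4.3.1 gives the outcome categories: "Response is defined as a more than 50% reduction in HAM-D17 scores", counted from inclusion. Remission is a HAM-D17 score of 7 or less.

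The Hamilton scale is in the flowchart row "Hamilton + MES + MAS + MDI + UKU + WHO-5", marked at every visit including week 29. For another association, cortisol with depression scores, section 11 names a rank method: "calculated by means of the Spearman correlation coefficient".

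Section 12 gives the number of patients: "it is intended to include 100 patients into the study, 50 to each group".

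**The concern.** The hypothesis is about a graded quantity, and section 2.3 expects a graded relation between the amount of exercise and the course of the depression. The planned test cuts both sides of that relation into categories. Response measures change from inclusion, and remission is one threshold on the week-29 score, so differences within a category do not count. If the chi-square is the ordinary Pearson test, the order of the three grades is not used either.

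Two things are at stake. First, a moderate association could well be missed in a group of 50. Second, exercise intensity is adapted to each patient (section 2.3), so the amount done in follow-up phase I is partly self-selected. Patients who are less depressed early on may exercise more and also do better at week 29, and the planned comparison makes no adjustment for early severity.

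**Working it through.** **Inputs from the protocol.** Group B has 50 planned patients (section 12). The type I error is 0.05 (section 11); it is not said whether this is one- or two-sided, and two-sided is used here. Section 11 does not name the analysis set for this test. Group B is taken because only that group is prescribed exercise.

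**Assumed, because the protocol gives no figure.** The true correlation between exercise and week-29 severity is 0.3, 0.4 or 0.5. Grades are equal thirds. The outcome is cut at its median, with other cuts tried below. No week-29 data are missing.

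**The plan's own figure first.** Section 11 states: "With a type-I error of 0.05 and 0.90 power, 39 patients are required for each group". This is for the week-9 HAM-D17 comparison of 10 with 13, SD 4. By normal approximation n = 2 × (1.960 + 1.282)² × 4² / 3² = 37.4, so 38. The two-sample t-test gives power 0.897 at 38 and 0.905 at 39, so 39 is reproduced. No power or sample size is stated for the exercise association.

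**Model.** Exercise x is standard normal and severity is y = −ρx + √(1 − ρ²)·e, with e standard normal. Each scenario was simulated at least 3,000 times, with three tests:
- Pearson chi-square on the 3x2 table: Σ(O − E)²/E, 2 df.
- Ordered trend on the same table: (n − 1)r², 1 df, where r is the correlation of grade (1, 2, 3) with outcome (0, 1).
- Spearman on uncut values: t = r√[(n − 2)/(1 − r²)], n − 2 df.

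**Power at n = 50, median outcome cut:**

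| True correlation | Pearson 3x2 | Ordered trend | Spearman, uncut |
|---|---|---|---|
| 0.3 | 0.25 | 0.34 | 0.52 |
| 0.4 | 0.43 | 0.55 | 0.78 |
| 0.5 | 0.65 | 0.78 | 0.95 |

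Repeat runs agree to within about 0.03. With no association, all three tests reject in about 5% of runs.

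**Other readings, correlation 0.4, n = 50.** Response/remission rates of 40/10%, 50/30%, 60/40% and 75/50% were tried:
- grades by response: 0.35 to 0.45
- grades by remission: 0.20 to 0.44
- grades by a three-level outcome (non-response, response, remission): 0.34 to 0.38
- Spearman on uncut values: 0.77 to 0.80

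Uneven grades (20/60/20, 50% response) give 0.41 for response. With 39 patients, response gives 0.30 to 0.35 and Spearman 0.66 to 0.69. At 50% response the Pearson 3x2 test needs about 110 patients for 0.80 power, against about 50 for Spearman.

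**Early severity.** As an illustration, suppose exercise has no effect on outcome, and early severity correlates 0.5 in size with both exercise and outcome. With n = 50 the Pearson 3x2 test is then significant in about 17 to 18% of runs, unadjusted Spearman in 38%, and a regression adjusted for early severity in 5%. An uncut analysis without adjustment would therefore be more exposed to this than the planned one.

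**The case against.** The strongest defence is that the test does address the hypothesis, in the protocol's own efficacy measures. Section 2.2 itself describes response as a halving of the degree of depression, and remission is a severity threshold at week 29. This stands. A reader might infer that the hypothesis goes untested, but the documents support only that it is tested coarsely.

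A reader might also infer that severity at the start is ignored. For response that is wrong, because inclusion HAM-D17 is the denominator. Remission does not use it. What remains is that neither category is adjusted for severity early in treatment.

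Section 11 does not say that the chi-square is unordered or that the outcome has only two levels. A trend test is also referred to a chi-square distribution, and such detail may sit in an SAP. At correlation 0.4 the trend test recovers 0.55 − 0.43 = 0.12 of the 0.78 − 0.43 = 0.35 gap. The other 0.23 remains.

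The Spearman figures are for an unadjusted test and must not be read as the power of the adjusted analysis proposed below. If severity correlates 0.3 in size with exercise and 0.4 with outcome (both assumed), an apparent 0.4 becomes (0.4 − 0.3 × 0.4)/√[(1 − 0.09)(1 − 0.16)] = 0.32, with power about 0.6.

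Finally, section 11 gives no formula for the combined exercise score. That is a fair limit, but grading the score presupposes that one exists.

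**Conclusion.** The point holds as a minor one. The planned test answers a question about degree of depression through coarse categories and gives up power. With 50 patients and an assumed correlation of 0.4, power is about 0.43 (Pearson 3x2) or 0.55 (ordered trend), against 0.78 for an unadjusted rank correlation on uncut values. The size rests on the assumed correlation, grades and outcome cut. The direction was the same in every scenario with a true association.

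A significant result may partly reflect less depressed patients exercising more. That is a limit on interpretation; the protocol itself asks only about an association.

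A reader might infer that the trial's main conclusion or its false-positive rate is at risk. The documents do not support that: the parameter is tertiary, the stated sample size does not rest on it, and the test keeps its 5% level when exercise and outcome are unrelated.

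**What to change.** In section 11, for Group B, analyse week-29 HAM-D17 against the uncut combined phase-I exercise score by linear regression adjusted for HAM-D17 at inclusion, or by partial Spearman correlation. Write down how the combined score is formed.

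Add week-2 HAM-D17 as a further covariate in a sensitivity analysis only. Exercise starts during the week-1 hospitalisation, so the week-2 score may already carry part of its effect.

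Keep the table of light/moderate/intensive by response and remission as description.

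The cost is a change of wording and a little more analysis work. The plan already collects the data, and no visits or patients are added.
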